## 3. Expected Impact

Although it is premature to allude to the outcomes, this section describes the expected impact of the study, aware that it must wait for the conclusion of the study to obtain the final result. The recent improvements in oncological therapies are progressively increasing the life expectancy of cancer patients [36]. This population constitutes a growing cohort at heightened cardiovascular risk for several reasons: the presence of concurrent risk factors, the pathophysiology of the underlying cancer, and several adverse cardiovascular effects of chemoradiation and other targeted therapies. Optimizing the cardiovascular health of cancer patients is an increasing healthcare priority requiring special considerations. Recent research has focused on the development of cardiovascular risk assessment tools tailored specifically for cancer patients. These tools could be used to identify individuals at high risk, prioritize preventive interventions, and monitor and manage cardiovascular risk in cancer patients over time. Overall, it is clear that the cardiovascular health of cancer patients should be a priority for healthcare providers. The use of telemonitoring assessment tools can help to manage the risk of cardiovascular events in advanced cancer patients with multiple comorbidities.

We expect that the results of this study may improve scientific knowledge regarding the impact of telemonitoring and telemedicine systems on QOL and psychological well-being in advanced cancer patients with relevant cardiovascular and respiratory comorbidities assisted at home.

Several studies regarding telemedicine in advanced cancer patients have regularly assessed psychosocial constructs and QOL [7]. Thus, previous studies and reviews reported a significantly higher QOL in telemedicine and telemonitoring interventions rather than in standard care [37,38]. Patients may receive significant support and comfort if their physicians provide them with timely and ongoing feedback on their health. One reason for the improvement of QOL is the capacity of telemedicine to reduce the geographical barrier between patients and clinical staff [38]. Moreover, the constant and continuous monitoring of vital parameters at every stage of the disease or whenever required could reduce suffering and anxiety, improving QOL. However, in this field, it is difficult to have a clear vision [7], whereas many tools could be included within telehealth and information technology (e.g., mobile phone devices, internet-based interventions, interactive health communication applications, virtual programs of support, and symptom monitoring tools) [8]. Specifically, our feasibility study may help to figure out if this telemonitoring tool is useful for advanced cancer patients assisted at home in order to increase the knowledge about the more appropriate telehealth intervention for this specific group of patients. A previous study suggested that the attention provided by telemedicine to patients with advanced cancer is helpful for maintaining quality home care [39]. In addition to reducing the impact of distance, we expect our practice could foster continuous healthcare delivery and closer communication among physicians, patients and families.

As the disease progresses, clinical condition changes and rapidly worsens; thus, adjustments and orientations are necessary to provide good care [39,40]. The daily and constant monitoring of patients’ vital parameters, albeit remotely, may enable the physician to have a clear and updated overview of the clinical trajectory of the disease and its symptoms. On the other hand, the patient may have the feeling of being constantly supported and assisted, significantly lowering distress and anxiety factors and increasing QOL. Indeed, using telemedicine, patients with significant symptoms of distress may receive a high-quality assessment and management of suffering from the comfort of their home without being compelled to move [41].

We expect a significant level of engagement in terms of the number of self-measurements/week per patient, ease of use, difficulties experienced, and usefulness. In this feasibility study, engagement will be evaluated by some indicators as defined by Perski et al., 2017 (and echoed by Goodman et al., 2022), including the frequency and duration of measurements, depth of device use, and others [8,42].

Furthermore, this telemonitoring intervention may have a positive impact on the caregivers. Improving advanced cancer patients’ QOL and psychological symptomatology may relieve the care burden perceived by caregivers and enhance the family’s satisfaction with the care received from the healthcare team. Indeed, previous studies stated that the caregiver’s QOL is related to the patient’s [43], making clear that a possible strategy for enhancing the caregiver’s QOL is to improve the patient’s [44]. In addition, telemedicine may help family caregivers to maintain their personal habits and professional position and to limit financial consequences due to missed workdays required to accompany their loved ones to medical clinics or hospitals [45].

In the present setting, one of the motivations sustaining the advantages of telehealth implementation is the potential to lower home care costs, as well as to improve and expand access to healthcare services [45]. Telehealth could impact costs by relieving the healthcare team from some clinical activities, such as the monitoring of vital parameters at home and reducing travel and workload [45].

The evaluation of secondary outcomes, such as the intensity of doctor/nurse home visits, phone calls, hospital admissions, and hospitalization days, will return an indirect measure of the impact of this telemonitoring intervention in terms of costs and suitability of resources provided by home care services and the National Health System.

## Figures and Tables

**Figure 1 jcm-12-01922-f001:**
[figure not shown]
Flow diagram of the study. ANT: National Tumor Assistance Foundation.

**Figure 2 jcm-12-01922-f002:**
[figure not shown]
ButterfLife medical device.

**Table 1 jcm-12-01922-t001:** Inclusion and exclusion criteria for eligible participants.

Inclusion Criteria
Men and women with solid and hematologic malignancies in an advanced stage, i.e., a locally advanced or metastatic cancer disease that is unlikely to be cured or controlled with treatment.
Aged ≥ 18 years.
Able to understand the objectives of the study and sign the informed consent.
Able to speak and understand the Italian language.
Karnofsky Performance Status (KPS) ≥ 50.
Presence of at least one of the following comorbidities: ⋅ Chronic obstructive pulmonary disease (COPD); ⋅ Chronic ischaemic heart disease (CIC) after acute myocardial infarction (AMI); ⋅ Pulmonary emphysema; ⋅ Valvulopathy; ⋅ Systemic arterial hypertension; ⋅ Severe coronary artery disease; ⋅ Respiratory failure related to primary or metastatic lung cancer disease; ⋅ Cardiomyopathy developed after oncological treatment. This symptomatology may be directly related to the oncological disease or independent of it (pre-existing pathology at the time of cancer diagnosis, symptoms occurring as a result of oncological therapies, or age-related onset). The severity of these comorbidities must be relevant to the patient’s clinical profile as expressed in at least one of the following conditions: ⋅ Resting oxygen saturation level <90% in room air or oxygen therapy; ⋅ Systolic/diastolic blood pressure greater than 140/90 mmHg or less than 90/60 mmHg, or on antihypertensive medication; ⋅ Resting heart rate greater than 100 or less than 60 beats per minute or being treated with anti-arrhythmic drugs or the presence of a pacemaker.
**Exclusion criteria**
Patients with a diagnosis of dementia or cognitive impairment hampering the comprehension of the study information and/or signing of informed consent.
End-of-life patients.
Patients refusing to participate.

**Table 2 jcm-12-01922-t002:** Questionnaires during the eight weeks of monitoring time. Supplementary Document 2 includes all the questionnaires administrated to patients and caregivers by the physician on Day 1, Day 28 and Day 56.

Timeline	Day 1	Day 28	Day 56
Patient	EQ-5D-3L DASS-21	EQ-5D-3L DASS-21	EQ-5D-3L DASS-21 Evaluation of the ButterfLife device *
Caregiver	CBI	CBI	CBI FAMCARE-2

EQ-5D-3L: EuroQoL-5D-3L questionnaire; DASS-21: Depression Anxiety Stress Scales-21; CBI: Caregiver Burden Inventory; FAMCARE-2: Family Satisfaction with Advanced Cancer Care-2; * Only for patients in ButterfLife group.

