### 2.4. Recruitment and Randomization

The investigator will be the ANT physician in charge with the home care of the patient. During the first visit, after verifying the inclusion and exclusion criteria, the investigator (ANT physician) will explain the study to the patient and caregiver and propose their participation. If they consent, after collecting informed consent for participation and personal data management, the physician will contact the Research Department of the ANT Foundation to include the dyad (patient and caregiver) in the study.

Participants will be randomly assigned by the Research Department staff to the ButterfLife group (25 patients) or the Control group (25 patients) by randomization using an Excel-generated random number set. Investigators that will run the statistical analysis will be blinded to the randomization procedure.

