### 2.5. Procedures and Data Collection

The study will last eight weeks for each patient. On the first day (day 1), the investigator will ask the patient and his/her caregiver to answer the questionnaires.

For patients in the ButterfLife group, the investigator will deliver the ButterfLife device (Figure 2) at home and explain its use. ButterfLife is a medical device similar to a joypad, designed by the Unimore spinoff VST (Vital Signal in a Touch, VST Srl, Modena, Italy), which, through the use of three different sensors, a photoplethysmogram, electrocardiogram, and an infrared thermometer, simultaneously measures the five primary vital parameters defined by the World Health Organization in 90 s (heart rate, respiratory rate, blood oxygenation, blood pressure, and body temperature). The ButterfLife device is designed to make self-measurements and therefore requires no external intervention for measurements. To record these parameters, the patient has to place both hands on the device, and the data collected are immediately transmitted to a portal whose software (VST-FIVE) calculates the vital signs and allows visualization of the sharing with the doctor via a Wi-Fi network (https://my.vital.st/) (accessed on 22 December 2022). To guarantee a stable internet connection, a 4G LTE Wi-Fi Router (TP-Link, Hong Kong) will be provided at the patient’s home. In this way, it is possible to ensure the early detection of worsening and failure of the health state, enabling the timely activation of appropriate intervention in the home setting. The recorded data remains available for subsequent evaluation, long-term monitoring, and offline analysis. The patient is recommended to take the measurement once a day, preferably in the morning, and to repeat the measurement of parameters during the day if necessary. The investigator will leave a booklet containing simple written instructions with images explaining the use of ButterfLife. The doctor will check the data recorded by the patient every day (Supplementary Document 1) and the trend of the parameters over time by a graphical representation on the electronic medical record (Vitaever, Nethical Srl, Bologna, Italy) (https://www.vitaever.com/) (accessed on 20 December 2022). Daily telemonitoring will be conducted in addition to standard home care.

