The quality of life (QOL) of patients will be assessed by the EuroQoL-5D-3L questionnaire (EQ-5D-3L), Italian version [27,28], a generic instrument consisting of 2 distinct sections: patient’s subjective assessment of five dimensions of quality of life (mobility, self-care, daily activities, pain/discomfort, and anxiety/depression); each item has responses graded from 1 to 3, where level 1 indicates no problems and level 3 indicates extreme limitation. Assessment of the patient’s perceived health status will be made on a visual analogue scale (VAS) graded from 0 (the worst possible health status) to 100 (the best possible health status).The psychological status of the patient will be evaluated by the Depression Anxiety Stress Scales-21 (DASS-21), Italian version [29,30], a self-assessment scale to detect depression, anxiety and stress. The scale consists of 21 items, 7 for each emotional state, assessed on a 4-point Likert scale (from 0 = never to 3 = always).Care burden perceived by the caregiver will be assessed by the Caregiver Burden Inventory (CBI) [31], a questionnaire consisting of 24 questions on 5 domains (time-dependent care burden, developmental burden, physical burden, social burden, and emotional burden). Completion requires ticking the box from 0 to 4 (0 = not at all, 1 = slightly, 2 = moderately, 3 = quite a lot, 4 = very much) that best describes the current condition or personal impression of the caregiver. The total score ranges from 0 to 100, where 100 indicates the highest perceived caregiver burden.Satisfaction with care stated by the caregiver will be assessed through the Family Satisfaction with Advanced Cancer Care-2 questionnaire (FAMCARE-2), Italian version [32,33], a specific validated instrument to measure family members’ satisfaction with the care received from a palliative care team for their relative with advanced cancer. The FAMCARE-2 consists of 17 questions whose answers, on a 5-point ordinal score ranging from 1 (very dissatisfied) to 5 (very satisfied), cover 5 domains (management of symptoms and patient comfort, information provided, support to the family, and psychological assistance to the patient). The total FAMCARE-2 score can range from 17 to 85, where 85 represents the highest satisfaction with the care received.

The total monitoring time will be 8 weeks: at day 1, after 4 weeks (day 28), and 8 weeks (day 56), the administration of questionnaires to the patient and caregiver will be repeated (Table 2).

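### The treating physician, who knows the arm, collects every questionnaire, which puts the Day 56 device evaluation and FAMCARE-2 at risk of courtesy bias

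*Protocol article*

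**What the plan says.** All places are in the protocol article.

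- **Who collects.** The legend of Table 2 says the questionnaires are "administrated to patients and caregivers by the physician on Day 1, Day 28 and Day 56".
- **Who that person is.** Section 2.4: "The investigator will be the ANT physician in charge with the home care of the patient".
- **What that person knows.** Section 2.5: "For patients in the ButterfLife group, the investigator will deliver the ButterfLife device (Figure 2) at home and explain its use". On follow-up it adds: "The doctor will check the data recorded by the patient every day".
- **What is collected at Day 56.** Table 2 lists EQ-5D-3L and DASS-21 for the patient, and CBI and FAMCARE-2 for the caregiver. Patients in the ButterfLife arm also evaluate the device. FAMCARE-2 and the device evaluation appear at Day 56 only.
- **What the two forms feed.** Section 2.6 describes the device evaluation in the primary-outcome paragraph, and Section 2.10 analyses it under acceptability and feasibility. FAMCARE-2 measures "satisfaction with the care received from a palliative care team" and is compared between arms in Section 2.10.
- **Blinding.** Sections 2.4 and 2.10 blind those who analyse the data, and nobody else.
- **Order of events.** Section 2.4 says that, after consent, "the physician will contact the Research Department of the ANT Foundation to include the dyad (patient and caregiver) in the study", and then describes random assignment by Research Department staff. Section 2.5 follows: "On the first day (day 1), the investigator will ask the patient and his/her caregiver to answer the questionnaires".

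**The concern.** Patients and caregivers who depend on a physician for home care are asked by that same physician how good the device is that he or she supplied, and how satisfied they are with the team to which he or she belongs. People in that position tend to answer kindly. Blinding the analysts does nothing about this, because the answers are already shaped when they reach the analysts.

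What is at stake is the pilot's reading of acceptability, which is the aim of the trial, and one between-arm secondary comparison. A smaller matter is the Day 1 measurement. If the arm is already known when it is taken, hope or disappointment about the allocation can enter the starting point of the time trend.

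**Working it through.** The plan gives no figure for this risk, so the check is mainly a reading of the passages together.

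**Step 1. Can the collector be blind?** The collector (Table 2 legend) is the investigator, who is the treating physician (Section 2.4). That person hands over and explains the device in one arm only (Section 2.5), so the answer is no. This holds even if the doctor who looks at the daily readings were someone else.

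**Step 2. Device evaluation.** Let T be the respondent's true opinion and c the courtesy shift. The recorded score is T + c. There is no control arm and no earlier measurement to subtract, so the bias in reported acceptability is the whole of c.

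**Step 3. FAMCARE-2.** With arms B (ButterfLife) and C (control), the compared difference is (T_B + c_B) − (T_C + c_C) = (T_B − T_C) + (c_B − c_C). Courtesy common to both arms cancels, and only c_B − c_C remains. A non-zero difference is plausible, because one arm has received something extra from the physician, but the document gives nothing from which to estimate it. There is no Day 1 FAMCARE-2 against which a shift could be checked.

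**Step 4. Sensitivity of the FAMCARE-2 test (assumed values only).** Inputs are 25 per arm and a Mann–Whitney test (Sections 2.9 and 2.10). Taking the efficiency relative to the t-test as 3/π, the effective size per arm is 25 × 3/π = 23.87, with df = 2 × 23.87 − 2 = 45.75 and noncentrality δ = d × √(23.87/2) = 3.455d.

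- Check against the plan's own figure: d = 0.8 gives δ = 2.764 and power 0.859 at one-sided α = 0.05. This reproduces the stated 0.86. (Two-sided, it is 0.772. That is a separate matter.)
- The same formula with no true effect and an assumed c_B − c_C, at two-sided 0.05:

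| Assumed differential shift (SD) | Chance of a significant result |
|---|---|
| 0.1 | 6% |
| 0.2 | 10% |
| 0.3 | 17% |
| 0.4 | 27% |
| 0.5 | 39% |

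The table assumes that all 25 caregivers per arm return the form. It shows how sensitive the test would be and does not estimate what will happen. It cannot be applied to the device evaluation, which has no between-arm effect.

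**Step 5. Which measures are not touched?** The percentage of eligible patients who agree to take part, and the weekly number of self-measurements, do not depend on who collects questionnaires.

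**Step 6. Day 1.** Section 2.4 describes inclusion and assignment. Section 2.5 then describes the Day 1 questionnaires and, next, device delivery to patients already in a group. If the arm is known at that moment and shifts the Day 1 score by a, the change from Day 1 to Day 56 is recorded as the true change minus a. This concerns EQ-5D-3L, DASS-21 and CBI, which Section 2.10 models over time. It cannot concern FAMCARE-2.

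**The case against.** The other side has five arguments.

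1. **These are self-ratings.** DASS-21 is self-assessed, CBI is a tick-box form, and Section 2.5 has the investigator ask for answers rather than score them. Section 2.8 reports training to standardise procedures. This stands in part: the physician can act only through presence and prompting. Training makes physicians alike, but it does not change the respondent's dependence on the physician who asks.
2. **Participants know their arm anyway.** This stands. Another way of collecting the forms lowers the risk but leaves what comes from the open design.
3. **The main measures of this pilot are safe.** This is true of the consent percentage and the measurement count. It is not true of the device evaluation, which sits beside them in the acceptability analysis.
4. **The baseline order is not stated.** This stands. A reader might infer that Day 1 scores are taken after allocation is known. The order of the sections suggests it, but no sentence says so. Within Section 2.5 the questionnaires are mentioned before device delivery, and the flow diagram (Figure 1) is not shown. A reader might also infer that a baseline-adjusted effect would be weakened, but Section 2.10 describes no baseline adjustment. Only the time trend is in question.
5. **Recruitment is under way.** A change now mixes collection modes in a small trial. This is a real but small cost if the change applies to both arms from one date.

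**Conclusion.** The point holds as a risk of bias in two Day 56 measures. The device evaluation is the more exposed, because nothing offsets a courtesy effect there. For FAMCARE-2, only the part that differs between arms matters.

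The size cannot be derived from the document. A reader might go further and conclude that the self-reported outcomes are biased, or express an assumed shift as a share of the planned effect size of 0.8. The documents support neither. They show that the collector is unblinded and has a stake in the answers, but not that answers are in fact shifted or by how much.

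The conclusion rests on the Table 2 legend meaning what it says, namely that the physician administers every form at every visit. The Day 1 point is secondary and conditional: it applies only if allocation is in fact known when those questionnaires are answered.

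**What to change.** **Main change.** Have the device evaluation and FAMCARE-2 completed without the physician present and returned in a sealed envelope, or online, to the Research Department. Tell respondents that the care team will not see individual answers. Start on the same date in both arms (FAMCARE-2 in both, the device evaluation in the ButterfLife arm).

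**Cost.** Envelopes or a link, and no extra assessor. Expect some more blank items from frail patients, and a change of collection mode for those still to reach Day 56.

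**Secondary change.** State when the Day 1 questionnaires are taken relative to allocation. If allocation may already be known, take them at the consent visit, before the physician contacts the Research Department. This reorders one step at no cost and protects the Day 1 to Day 56 trend for EQ-5D-3L, DASS-21 and CBI.

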## Data Availability

Data are unavailable at the moment since the recruitment is in progress.
